## Abstract

**Background:**

With more than 15,000 new cases /year in France and 2,000 deaths, cutaneous melanoma represents approximately 4% of incidental cancers and 1.2% of cancer related deaths. In locally advanced (stage III) or resectable metastatic (stage IV) melanomas, medical adjuvant treatment is proposed and recent advances had shown the benefit of anti-PD1/PDL1 and anti-CTLA4 immunotherapy as well as anti-BRAF and anti-MEK targeted therapy in BRAF V600 mutated tumors. However, the recurence rate at one year is approximately 30% and justify extensive research of predictive biomarkers. If in metastatic disease, the follow-up of circulating tumor DNA (ctDNA) has been demonstrated, its interest in adjuvant setting remains to be precised, especially because of a lower detection rate. Further, the definition of a molecular response could prove useful to personalized treatment.

**Methods:**

PERCIMEL is an open prospective multicentric study executed through collaboration of the Institut de Cancérologie de Lorraine (non-profit comprehensive cancer center) and 6 French university and community hospitals. A total of 165 patients with resected stage III and IV melanoma, eligible to adjuvant imunotherapy or anti-BRAF/MEK kinase inhibitors will be included. The primary endpoint is the presence of ctDNA, 2 to 3 weeks after surgery, defined as mutated ctDNA copy number calculated as the allelic fraction of a clonal mutation relative to total ctDNA. Secondary endpoints are recurrence-free survival, distant metastasis-free survival and specific survival. We will follow ctDNA along treatment, quantitatively through ctDNA mutated copy number variation, qualitatively through the presence of cfDNA and its clonal evolution. Relative and absolute variations of ctDNA during follow-up will be also analyzed.

PERCIMEL study aims at provide scientific evidence that ctDNA quantitative and qualitative variations can be used to predict the recurrence of patients with melanoma treated with adjuvant immunotherapy or kinase inhibitors, thus defining the notion of molecular recurrence.

## Background

With an estimated 15,500 new cases in 2018 in metropolitan France (7,900 men and 7,600 women), and 1,880 deaths (1,040 men and 840 women), cutaneous melanoma accounts for around 4% of all incident cancers, and 1.2% of all cancer-related deaths among both sexes. It is one of the forms of cancer that has seen its incidence and mortality rise significantly in the last 40 years (data from the National Cancer Institute, www.e-cancer.fr). At locally advanced or metastatic stages, relative survival at 5 years is around 60% in patients with loco-regional cancer, and 15% in those with metastasis. At earlier stages of the disease, relative 5-year survival is above 90%, but although patients can be potentially cured by surgery, 13% will go on to develop loco-regional or metastatic disease within 2 years.

Standard treatment for locally advanced melanoma that is amenable to surgery (stage III disease) is surgical resection, with lymph node dissection in case of macroscopic lymph node involvement, or sentinel node biopsy in the absence of detectable macroscopic lymph node involvement. For metastatic melanoma (stage IV), metastasis amenable to complete surgical removal without residual disease should undergo surgery. In these cases, adjuvant medical therapy is proposed.

Since the advent of the first adjuvant treatments based on interferon α2b, the therapeutic arsenal has increased considerably, with immunotherapies such anti-PD1 [1, 2], and targeted therapies using the tyrosine kinase BRAF and MEK inhibitors for patients harbouring activating mutations of the BRAF gene [3].

Recently published analyses reporting 3 to 5-year survival have confirmed the value of adjuvant treatment for operable stage III and IV melanoma. Accordingly, in the randomized, phase III KEYNOTE-054 study, which investigated the anti-PD1 monoclonal antibody pembrolizumab versus placebo in resected high-risk stage III melanoma, the results showed a significant prolongation of recurrence-free survival (RFS) at 3 years (63.7% vs 44.1%, hazard ratio (HR), 0.56; 95% confidence interval (CI), 0.47 to 0.68) [4]. Similar findings were also reported from the randomized, phase III Checkmate 238 study, which tested the anti-PD1 monoclonal antibody nivolumab versus immunotherapy with the anti-CTLA4 monoclonal antibody ipilimumab in patients with resected stage IIIB–C or stage IV melanoma, and found a sustained RFS benefit in favour of nivolumab at 4 years (51.7% versus 41.2% with ipilimumab (HR, 0.71, 95% CI 0.60–0.86) [5]. In addition, in the randomized, phase III Combi-AD trial, evaluating the association of the BRAF inhibitor dabrafenib and the MEK inhibitor trametinib versus placebo in patients with BRAFV600 mutant melanoma, the results showed a significant improvement in RFS at 5 years, with 52% RFS in the dabrafenib plus trametinib arm versus 36% in the control group (HR, 0.51; 95% CI, 0.42 to 0.61) [6].

In a recent published paper, [7] the authors presented the results of a neoadjuvant and adjuvant or adjuvant only Pembroluzumab in locally advances melanoma. They included 313 patients, 154 in the neoadjuvant-adjuvant arm and 159 in the adjuvant only arm. All patients had clinically detectable measurable disease stage IIIB to IIID melanoma or oligometastatic resectable stage IV. Primary objective was EFS (Event Free Survival). With a median follow up of 14,7 months they demonstrated significant benefit for the neoadjuvant – adjuvant arm, with an EFS of 72% at 2 years versus 49% in the adjuvant arm with a *p* value at 0.004. This new strategy will be considered very soon as a standard of care, and needs to be integrated in our study, an amendment is in preparation.

However, the rate of relapse at one year after the end of treatment is around 30%, underlining the need to find predictive markers of early relapse [6].

In this context, analysis of circulating tumor DNA (ctDNA) is of relevance. The presence of nucleic acid in the blood was first described in 1948, but it has only recently been discovered that tumours are capable of actively and passively releasing their DNA into body fluids (for review, see [8]). Technological progress, notably in molecular biology, now makes it possible to detect ctDNA and to envisage clinical applications using ctDNA detection in the field of medical oncology. The detection of ctDNA, *i.e.* genetic material released by the tumour during necrosis, apoptosis or other active cell phenomena, could be used for the early detection of cancer, for theranostic applications, for follow-up of patients, to evaluate the quality of surgery or for the early detection of relapse [8]. Indeed, it has been shown that the concentration of ctDNA is correlated to tumour burden and consequently, is higher in patients with metastasis.

In the setting of melanoma, the majority of studies have been performed in metastatic, inoperable disease [9–17]), where ctDNA was more easily detectable, and frequently observed (70–90%).

These studies were performed in patients with non-resectable, stage III or metastatic (stage IV) melanoma, treated with BRAF inhibitors, with or without MEK inhibitors. The concentration of ctDNA before, and 4 weeks after treatment was shown to be a prognostic factor for survival [16]. Prior to the advent of adjuvant therapies, studies also showed the utility of ctDNA in operable advanced melanoma: ctDNA at 12 weeks after surgery seemed to be of use for predicting survival in patients with operable stage II or III melanoma [18], and also in patients with stage III disease, independently of the substage (a/b/c/d), when ctDNA was measured pre-operatively [19, 20]) or post-operatively [20].

A study of non-resectable advanced melanoma treated by immunotherapy or targeted therapy, with or without chemotherapy, showed that variations in ctDNA during follow-up were an indicator of treatment efficacy, suggesting that ctDNA could be a better reflection of tumoral heterogeneity than tissue biopsy [21].

In patients who undergo surgery, the situation is different, and notably, ctDNA can only be detected in a much smaller percentage of cases (20–40%). Few studies were performed before the advent of adjuvant treatment with immunotherapy or BRAF and MEK inhibitors. For example, the study by Tan et al. [20] in patients with operable, stage III melanoma found that the detection of ctDNA at baseline and after treatment was associated with shorter RFS and inferior distant metastasis-free survival (DMFS). In the same way, other studies [18, 19] performed respectively in 161 stage II/III high-risk melanoma patients and 174 patients with stage III melanoma undergoing complete lymph node dissection, found that the detection of ctDNA at baseline was associated with a higher rate of LN involvement, high lactate dehydrogenase (LDH) levels and worse melanoma-specific survival [19], and the presence of ctDNA post-operatively was associated with shorter metastasis-free and overall survival.

These studies also highlight the value of ctDNA for the prediction of survival in patients with operable stage II and III melanoma [18], and in stage III, regardless of substage (a/b/c/d) when ctDNA is measured at baseline [19, 20] or post-operatively [20]. More recently, the study by Gouda et al. [22] in 80 patients with BRAFV600E mutated melanoma of stage ≤ III, detection of ctDNA after surgery was associated with a higher likelihood of melanoma recurrence and shorter disease-free and overall survival. Furthermore, analyses of ctDNA from patients included in the Checkmate 915 study found that the presence of ctDNA predicted early relapse and inferior progression-free and metastasis-free survival, in patients with resected stage IIIB-D/IV melanoma receiving adjuvant nivolumab with or without ipilimumab [23]).

In these studies, which were almost all performed before the introduction onto the market of kinase inhibitors and immunotherapy in the adjuvant setting, none investigated normalized follow-up of ctDNA during treatment, or the link between the course of ctDNA and therapeutic response.

In the current era of adjuvant therapy, one of the aims of the PERCIMEL study is to determine whether the monitoring of ctDNA makes it possible to predict relapse, thereby defining the concept of molecular relapse.

## Objectives

The primary objective of PERCIMEL study is to evaluate the predictive value of the presence of ctDNA post-surgery on recurrence-free survival at 24 months in patients undergoing surgery for cutaneous melanoma and treated with immunotherapy or targeted therapy with BRAF and MEK inhibitors, in an adjuvant setting.

The secondary objectives are:To evaluate the predictive value of baseline (prior to surgery) ctDNA on survival (recurrence-free survival, distant metastasis-free survival and specific survival).To analyse the quantitative and clonal course of ctDNA during 24 months of follow-up, or at relapse, to predict survivalTo describe the clinical characteristics and the quantitative course of ctDNA during follow-up in patients with no detectable ctDNA at pré and/or post-surgeryTo determine the predictive value of ctDNA course in subgroups of patients according to clinical and tumour characteristics at inclusion.

## Method/design

The PERCIMEL study is an Interventional multicenter cohort study with minimal risks and constraints.

Figure 1 summarizes the study scheduling. The study is registered on ClinicalTrials.gov (NCT04866680), and French Competent Authorithy (ID-RCB: 022-A01904-39).

**Fig. 1 Fig1:**
[figure not shown]
Percimel protocol scheduling

### Study population

The PERCIMEL study is proposed to patients diagnosed with histologically-proven cutaneous melanoma, locally advanced, resectable, with complete lymph node dissection upfront in patients presenting with macroscopic lymph node involvement, or with positive sentinel lymph node biopsy (microscopic lesions) or surgery of distant metastasis, followed by adjuvant therapy with immunotherapy or targeted therapy with BRAF and MEK inhibitors, according to currently approved indications.

### Inclusion criteria

Patient aged 18 years or olderWHO performance status 0–2Patient with histologically-proven cutaneous melanoma, locally advanced (stage III) or metastatic and amenable to complete resection (stage IV)Naïve of all treatments (except for initial biopsy for diagnostic purposes)Patient with an indication for adjuvant therapy with BRAF and MEK inhibitors or immunotherapy with anti-PD1 monoclonal antibodies, according to currently approved indicationsBiological parameters compatible with the proposed treatmentPatient affiliated to a social security regimen, or beneficiary thereofSignature of informed consent form

### Non-inclusion criteria

Patients with mucous melanoma or choroidal (uveal) melanomaPatient presenting with a synchronous tumour, or having been treated in the 3 years prior to pre-inclusion (except for cervical carcinoma in situ, or resected cutaneous carcinoma)Patients with a contra-indication to blood draw of 30 mlPatients with a contra-indication to surgeryPatients with a contra-indication to the proposed adjuvant therapyPregnant or breastfeeding womenPatients under any form of judicial or legal protection

### Sample size calculation

Our hypothesis is that 25% of patients will have detectable ctDNA post-operatively, i.e. within 2 to 3 weeks after surgery [20].

Recurrence-free survival at 24 months in this population, based on key studies of adjuvant therapies, can be estimated at 70% (upper limit, to ensure a good statistical power) [1, 2, 24].

Based on an inclusion period of 24 months, an alpha risk of 5% and statistical power of 90%, a total of 124 patients would be required to achieve a hazard ratio of 2.5 [18, 20]. By considering 10% of patients lost to follow-up at 24 months or not analysable, then a total of 136 patients are necessary.

It is expected that almost all patients with stage IIIc/IIId/IV melanoma who are pre-included will subsequently be definitively included. Conversely, we estimate that around 70% of patients with stage IIIa-IIIb melanoma who are pre-included will have negative sentinel lymph nodes and therefore, will not be eligible for definitive inclusion. In view of the active pool of patients, we expect that stage IIIa-IIIb patients will account for 25% of all pre-included patients. Thus, to achieve definitive inclusion of 136 patients, we estimate that 165 patients will need to be pre-included.

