Baseline characteristics of the study population will be compared between patients with and patients without detectable ctDNA pre- and/or post-operatively. Qualitative variables will be compared using the chi square or Fisher’s exact test, and quantitative variables using the Student t or Mann–Whitney U test, according to whether the distribution of the variable is normal or not. Normality will be tested using the Shapiro–Wilk test. A multivariate logistic regression model will be fit to determine the characteristics that best distinguish the two populations. The discriminant power of the model will be determined using the area under the receiving operating characteristic (ROC) curve. In patients with no detectable ctDNA either pre- or post-operatively, the course of quantification of ctDNA will be described by repeated measure ANOVA using the mixed linear model, to take account of the correlation between measures in a same patient. Time will be considered as a fixed effect, and the patient as a random effect. The analysis will be performed in patients who have progressive disease, and those who do not.

The cut-off timepoint for this analysis will be the date of progression or end of follow-up. The values analysed will be number of copies of mutant DNA, taking account of all values obtained since inclusion.

All statistical analyses will be performed using SAS version 9.4 (SAS Institute Inc., Cary, NC, USA). A *p*-value < 0.05 will be considered statistically significant.

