### Follow-up visits (from 12 to 24 months)

All follow-up visits will be scheduled to coincide with the standard follow-up appointments, in order to avoid the patient having to attend visits solely for the purposes of the study. Follow-up visits will be planned according to current guidelines. For the purposes of the study, a follow-up visit will be planned every 6 months ± 2 weeks.

Appropriate, systematic radiological examination (CT or PET scan) is recommended every 6 months during the 12 months of follow-up.

Each follow-up visit will consist in:Complete clinical examinationAssessment of general state (WHO score) and body weightRecording of any adverse events grade > 2 or adverse events of any grade (according to the CTCAE classification version 5) if the impact on medical therapy or further management is significantRecording of concomitant treatments (if there are any changes compared to those recorded at the pre-inclusion visit)Tumour assessmentA blood draw of 30 ml for ctDNA analysis, performed on the day of each follow-up visit

After the 12 months of follow-up, the patient will have one final blood draw and will then exit the study.

In case of relapse during the 12 months of surveillance, the patient will have one final blood draw and will then exit the study.

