## Discussion

Recent results have been reported [23], showing that liquid biopsy proved suitable for follow-up of patients with stgae III B-D, IV melanoma, receiving adjuvant immunotherapy. In this translational study, baseline ctDNA positivity in resected stage III and IV melanoma was reported to be not highly prevalent (16%) and predictive of a poorer recurrence-free survival (HR 1.87) and distant-metastasis-free survival (HR 2.86). Further, baseline ctDNA combined with other biomarkers (tumor molecular burden, IFNγ) were more predictive of recurrence than any other biomarker alone.

In the landscape of studies investigating the predictive value of ctDNA for treatment response or prognosis in melanoma [25], the present PERCIMEL study has several original features:Standardized follow-up at key timepoints during management with blood tests performed, at baseline, prior to surgery; at the first post-operative visit; at initiation of adjuvant therapy; at each follow-up visit up during the 12 months of adjuvant therapy; at each follow-up visit during the 12 months of surveillance; at the time of occurrence of relapsePersonalized follow-up: to determine the genetic characteristics of the tumour, high-throughput sequencing of 517 genes known to be of interest in cancer will be performed on tissue samples from the initial lesion of each patient. The selection of 3 clonal and subclonal mutations per patient will make it possible to obtain a personalized follow-up marker for each patient, specific to each tumour. For each mutation, the use of tailor-made detection probes will enable personalized analysis by droplet digital PCR (ddPCR) during follow-up.Optimized technique: by partitioning samples into thousands of nanoliter-sized droplets, ddPCR enables the detection of variants with low allele frequency (0.005%), making it the most sensitive technique available today. This high sensitivity technique also enables the detection of any potential residual disease, both via monitoring of the DNA concentration in the plasma, and via the monitoring of tumoral clones and subclones specific to each patient.

PERCIMEL study is designed to provide scientific evidence that ctDNA can be used to predict the recurrence of patients with melanoma treated with adjuvant immunotherapy or kinase inhibitors, and to define the notion of molecular recurrence in resected stage III/IV melanomas.

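### At the stated 70% RFS, with every patient leaving at 24 months, 124 patients give about 78% or 86% power for a hazard ratio of 2.5, not the stated 90%

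*Protocol article*

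**What the plan says.** All planning inputs are in the protocol article, section Sample size calculation:

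- Prevalence: "Our hypothesis is that 25% of patients will have detectable ctDNA post-operatively".
- Event rate: "Recurrence-free survival at 24 months in this population, based on key studies of adjuvant therapies, can be estimated at 70" per cent. The text adds that this is an upper bound, chosen with power in mind.
- Error rates and accrual: "Based on an inclusion period of 24 months, an alpha risk of 5% and statistical power of 90" per cent.
- Result: "a total of 124 patients would be required to achieve a hazard ratio of 2.5". An allowance for losses then raises this to 136.

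The section gives no formula, sidedness, number of events or length of follow-up for the calculation.

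The follow-up is fixed elsewhere. The primary objective concerns RFS at 24 months. The section on visits from 12 to 24 months covers the year after the 12 months of adjuvant therapy and ends: "After the 12 months of follow-up, the patient will have one final blood draw and will then exit the study". The Statistical analysis section names the log-rank test, with Cox hazard ratios and 95% confidence intervals, and a p-"value < 0.05 will be considered statistically significant".

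**The concern.** The power of a log-rank test depends on the number of events. With 70% event-free at 24 months and nobody followed further, 124 patients yield 0.30 × 124 = 37 events, split over groups of 31 and 93. That looks too few for 90% power at a hazard ratio of 2.5.

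The section also lists a 24-month inclusion period as an input. Accrual time changes power only if early patients are followed beyond 24 months, and the visit schedule does not allow that. The calculation and the schedule may therefore rest on different follow-up.

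At stake is how a non-significant primary result is read. With 90% power it would count as fairly strong evidence against a hazard ratio of 2.5. With 78% power, such an effect would be missed more than one time in five.

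**Working it through.** **Inputs.** N = 124, of whom 25% (31) are ctDNA-positive and 93 negative; HR = 2.5; 24-month RFS 70%; alpha 5%; all patients censored at 24 months. Three things are assumed: two-sided testing (the text does not state it, but the 0.05 threshold and 95% intervals point that way), exponential times with proportional hazards, and no further loss among the 124.

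**Expected events.**

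- *70% is whole-cohort RFS.* Solve 0.75·S + 0.25·S^2.5 = 0.70. This gives S = 0.764 in negatives and 0.509 in positives. Events: 0.300 × 124 = 37.2.
- *70% is ctDNA-negative RFS.* Positives have 0.70^2.5 = 0.410. Event fraction: 0.75 × 0.30 + 0.25 × 0.590 = 0.3725. Events: 0.3725 × 124 = 46.2.

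**Can 124 be reproduced?** With (1.960 + 1.282)² = 10.507:

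- *Schoenfeld:* 10.507 / (0.25 × 0.75 × (ln 2.5)²) = 10.507 / 0.1574 = 66.7 events. Dividing by the event fraction gives N = 223 (whole cohort) or 180 (ctDNA-negative). It does not reproduce 124.
- *Freedman, 3:1 allocation, φ = 31/93 = 1/3:* 10.507 × (1 + φ·2.5)² / (φ × 1.5²) = 10.507 × 3.361 / 0.75 = 47.1 events. N is 157 (whole cohort) or 126 (ctDNA-negative). The second is close to 124.
- *Lakatos-type calculation, whole-cohort reading:* N = 162 with exit at 24 months. N = 122 with 24 months of accrual and at least 24 months of follow-up, so up to 48 months for the first patients. The second is close to 124.

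So two routes lead to about 124. One assigns the 70% to ctDNA-negative patients. The other needs follow-up that the visit schedule does not provide.

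**Power at 124 with exit at 24 months.**

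| Method | 70% = whole cohort (37 events) | 70% = ctDNA-negative (46 events) |
|---|---|---|
| Schoenfeld | 67.7% | 76.9% |
| Two-proportion | 75.1% | 82.4% |
| Simulated log-rank | 77-79% | 85-86% |
| Lakatos | 81.0% | 88.2% |
| Freedman | 82.2% | 89.4% |

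The simulation applies the planned test directly, so it is the figure to rely on. With 20,000 runs it gives 77.4% and 85.5%; repeated simulations stay within the ranges shown. Schoenfeld is pessimistic here and Freedman optimistic.

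**What 90% would take, by simulation.** About 182 evaluable patients (whole cohort) or 146 (ctDNA-negative). With N held at 124, the detectable HR is about 3.0 (simulated power 90.1%) or about 2.7 (90.9%). Schoenfeld puts these at 3.4 and 2.9.

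**Follow-up until the last patient reaches 24 months.** About 50 or 61 events, and simulated power of about 88% or 92%.

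**The case against.** The strongest reply is that 124 is not an arithmetic error. A standard approximation comes within two patients of it with exit at 24 months, and gives 89.4% power at 124. That stands. A reader might infer from the Schoenfeld figures that 124 cannot be derived, or that power is at most 68-77%; the calculation above does not support either. What the reply does not do is deliver the power. It needs the 70% to mean ctDNA-negative patients, whereas the text speaks of the study population and cites adjuvant trials, and the log-rank test itself has about 86% at that design.

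A second reply is that 70% is declared an upper bound, so more events are likely. This also stands. With exit at 24 months, simulated power on the whole-cohort reading is about 84% at 65% RFS, 87-88% at 60% and 90-91% at 55%. On the ctDNA-negative reading it is about 89% at 65% and 92% at 60%. The design may well reach 90% if outcomes are worse than planned. The stated 90% is nevertheless attached to 70%.

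A third is that a condensed article may leave the formula and event count to the full protocol. Fair, and their absence alone would not be a finding. The point is that the figures printed do not fit together.

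A reader might also infer a much larger shortfall from the Discussion, which reports 16% positivity and an RFS hazard ratio of 1.87 in another adjuvant immunotherapy study. At those values power would be about 29% (Schoenfeld) to 40% (simulated). But they are that study's baseline results, and the documents do not show that its sampling time or assay matches a patient-specific ddPCR test 2 to 3 weeks after surgery. They contradict nothing in the sample size section and can serve at most as a sensitivity line.

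**Conclusion.** The point holds in a limited form. For the inputs as printed, and with the 24-month exit as printed, the planned test has about 77-79% power if the 70% is whole-cohort RFS and about 85-86% if it is ctDNA-negative RFS. The shortfall is roughly 12 points on the literal reading and 4 to 5 on the favourable one. On the literal reading no two-sided method tried exceeds about 82%, and 124 is recovered only with follow-up that the visit schedule excludes.

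This rests on two-sided testing, proportional hazards, exponential times and an exact 25:75 split. One-sided 5% testing would give about 85% and 91% in simulation, but nothing in the text indicates it. The documents do not support the stronger conclusion that the trial is badly underpowered whatever happens, because RFS below the stated upper bound brings power up to 90%. The stated power should be corrected; the design need not be abandoned.

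**What to change.** In the Sample size calculation section:

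1. State which group the 70% describes.
2. State the follow-up assumed, and reconcile it with exit at 24 months. If follow-up stops there, say that the inclusion period plays no part in the power.
3. Name the method and sidedness, and give the expected events (about 37 or 46).
4. Restate the power at 124 patients for HR 2.5 (about 78% or about 86%), and the HR detectable with 90% power (about 3.0 or about 2.7 by simulation).
5. Add a short sensitivity line for RFS below 70% and, if wished, for 16% prevalence with HR 1.87, labelled as another study's values.

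The cost is a few sentences and a less favourable stated power.

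Optionally, collect recurrence dates from routine records until the last included patient reaches 24 months. Simulated power then rises to about 88% or 92% with the same 124 patients. This needs data on earlier patients after their study exit and goes beyond the 24-month horizon of the primary objective. It does not fully restore 90% on the literal reading.

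### The 10% loss allowance is applied as 124 × 1.10 rather than 124 / 0.90, so 136 inclusions fall slightly short of the plan's own 124; separately, the abstract presents the 165 pre-inclusions as inclusions

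*Protocol article*

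**What the plan says.** The Sample size calculation section of the protocol article builds its numbers in three steps.

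- Base requirement: "a total of 124 patients would be required to achieve a hazard ratio of 2.5".
- Loss allowance: "By considering 10% of patients lost to follow-up at 24 months or not analysable, then a total of 136 patients are necessary".
- Pre-inclusion: nearly all stage IIIc, IIId and IV patients are expected to go on to definitive inclusion, while about 70% of stage IIIa-IIIb patients are expected to have negative sentinel nodes and drop out before it. On the mix of stages, "we expect that stage IIIa-IIIb patients will account for 25% of all pre-included patients". The section concludes: "we estimate that 165 patients will need to be pre-included".

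The Inclusion visit section confirms that pre-included patients whose nodes or metastases are not confirmed leave the study at that point. The Methods paragraph of the abstract, however, gives the size of the study as "A total of 165 patients with resected stage III and IV melanoma", describes these patients as eligible for adjuvant treatment, and says that they will be included.

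**The concern.** Two things do not fit together.

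First, a loss rate of 10% is a share of the patients who are included. To keep 124 after that loss, the number included must be 124 divided by 0.90. The stated 136 is what results from adding 10% of 124 to 124, and removing 10% of 136 does not lead back to 124. Because the pre-inclusion number is computed from 136, it carries the same shortfall.

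Second, the abstract and the body attach the number 165 to different groups. The body separates pre-inclusion from definitive inclusion throughout, so this is more than loose wording: a reader of the abstract alone would take the wrong sample size.

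At stake are the internal consistency of the recruitment target and the number that readers will cite as the size of the trial.

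**Working it through.** **Inputs, all from the Sample size calculation section:** 124 patients required; 10% lost or not analysable; 25% of pre-included patients at stage IIIa-IIIb; about 70% of those not going on to inclusion; nearly all other patients going on, taken here as 100%.

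**Reproducing the plan's figures**

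- Loss allowance: 124 × 1.10 = 136.4, which gives the stated 136 when rounded down. Rounded up, the same method would give 137.
- Share of pre-included patients reaching inclusion: 0.75 × 1 + 0.25 × 0.30 = 0.825.
- Pre-inclusions: 136 / 0.825 = 164.8, which gives the stated 165.

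**What the stated numbers deliver**

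- From 136 inclusions: 136 × 0.90 = 122.4.
- From 165 pre-inclusions: 165 × 0.825 = 136.1 inclusions, and 136.1 × 0.90 = 122.5.

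Both are about 1.5 patients below 124, so rounding up to 165 does not absorb the gap.

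**What the plan's own loss rate requires**

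- Inclusions: 124 / 0.90 = 137.8, so 138. Check: 138 × 0.90 = 124.2.
- Pre-inclusions: 138 / 0.825 = 167.3, so 168. Check: 168 × 0.825 × 0.90 = 124.7. With 167 the result is 123.998, just under 124.

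**Effect on power.** Take the plan at its word that 124 gives 90% power, and assume a two-sided 5% test (the article does not state the number of sides). Events scale with the number of patients, so the standardised effect shrinks by √(122.4 / 124) = 0.9935. From 1.960 + 1.282 = 3.242 it falls to 3.221. Power becomes Φ(3.221 − 1.960) = Φ(1.261) ≈ 0.896, a loss of about 0.4 points.

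**The abstract.** Expected exits before definitive inclusion: 165 × 0.25 × 0.70 = 28.9, about 29. The difference 165 − 136 is also 29, and 165 / 136 = 1.21, so the abstract's figure exceeds the planned number of definitive inclusions by 21%.

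**The case against.** The best case for leaving the text alone has three parts.

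*The gap is trivial.* Multiplying by one plus the loss rate is common shorthand, and at 10% it differs from the correct division by two patients. The inputs to the pre-inclusion step are themselves approximate. This stands as a statement about size. It does not make 136 consistent with 124 and a 10% loss.

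*About 122 is a worst case.* A reader might infer that the trial will analyse only 122 patients. The documents do not support that. The 10% combines patients lost by 24 months with patients who are not analysable, and the article does not give the split. The Statistical analysis section uses Kaplan–Meier, log-rank and Cox methods, in which a patient lost early is censored and still contributes time at risk. Only the non-analysable part is removed outright, for example patients with no post-operative sample, which the Premature withdrawal section lists as a reason for leaving the study and without which the primary comparison cannot classify them. The plan does count both groups as lost when it sets the target, so 122 is the right figure on its own accounting, but it is not a forecast of the analysis set.

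*The base of 124 matters more.* This is fair. With the 70% recurrence-free survival placed in the ctDNA-negative group, a fixed 24 months of follow-up and a two-sided test, a Freedman calculation for unequal groups gives about 126. A Schoenfeld calculation gives about 179, or about 223 if the 70% applies to all patients. Moving from 136 to 138 does not settle that separate question and should not be presented as having repaired the sample size.

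On the abstract, a reader might infer that it overstates the analysed cohort by 29. It does not call 165 the analysed number, and 136 is not that number either, because it still contains the loss allowance. The valid comparison is 165 with 136 definitive inclusions. The body resolves the discrepancy for anyone who reads it, but the abstract remains wrong as written.

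**Conclusion.** The point holds as a minor arithmetic error. The allowance was applied as 124 × 1.10, and the stated targets deliver about 122 fully evaluable patients against the 124 required: 2 inclusions and 3 pre-inclusions short, with about 0.4 points of power lost. This rests on three assumptions: that 124 is sound, that all of the 10% is lost to the analysis, and that every stage IIIc, IIId or IV patient goes on to inclusion. Relaxing the second makes the gap smaller; relaxing the third makes it slightly larger. It does not threaten the trial, and it is no ground for calling the trial underpowered.

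The abstract's use of 165 is a separate inconsistency, unrelated to the loss allowance, and its 21% should not be read as the size of the arithmetic error.

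**What to change.** For the loss allowance, choose one:

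- keep 136 definitive inclusions and 165 pre-inclusions, and state that about 122 fully evaluable patients are expected if all of the 10% are lost; or
- restate the targets as 138 definitive inclusions and 168 pre-inclusions.

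In the abstract, give the size as 165 pre-included and about 136 definitively included (168 and about 138 under the second option), and describe neither as the analysed cohort.

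The cost is a few edited numbers and, under the second option, three more pre-inclusions. The Background section says that an amendment is in preparation, and the changes could go into it.
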